### Objectives

Primary Objective: To determine whether photobiomodulation combined with a new photopolymerizable resin improves hypersensitivity in MIH-affected carious molars.

Secondary objectives:

To compare the effectiveness of three interventions: photobiomodulation combined with self-cure resin, self-cure resin alone, and photobiomodulation combined with bulkfill photopolymerizable resin in controlling hypersensitivity over time.To assess the clinical performance of the self-cure composite resin in terms of restoration longevity.

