#### Clinical assessment.

The clinical assessment will be performed by an examiner blinded to the allocation of the teeth to the different groups. The criteria will be the retention of the restorative material in the cavity, posteruptive breakdown of the enamel adjacent to the restoration and the occurrence of secondary caries. The criteria of the modified USPHS index will be used for the assessment. The restoration will be characterized as a failure and the tooth will be excluded from the study if the C score is determined for any of the USPHS criteria [27]. Photographs will be taken using a digital single-lens reflex (DSLR) camera (Canon EOS 700D; Canon, Tokyo, Honshu, Japan) to complement the clinical data. These photographs will be taken before and after the restorative treatment, as well as during all follow-up periods, following the same standardized parameters. This will ensure consistency in clinical data collection. The visual demonstration will contribute to any necessary clarifications and make the discussion and documentation of the cases more efficient [28].

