### Statistical analysis

The data will be presented using descriptive statistics. Continuous variables will be described with mean and standard deviation, and categorical variables by relative frequency. Statistical analyses will be conducted using SPSS software (version 28.0, IBM, USA). For comparisons of the Wong-Baker Faces Pain Rating Scale and SCASS scales, a repeated measures analysis of variance (ANOVA) will be used, considering the three groups and five time points of the study. This analysis will address the objective of comparing the effectiveness of interventions in controlling hypersensitivity over time. Post-hoc comparisons will be made using the Bonferroni adjustment to control for Type I error in multiple comparisons. The normality of the data distribution and the homogeneity of variance will be confirmed by the Shapiro-Wilk and Levene tests, respectively. The presence of sphericity will be verified using the Mauchly test, and if violated, corrections such as Greenhouse-Geisser will be applied. For secondary outcomes, repeated measures ANOVA will also be used to compare differences over time among the three intervention groups. Post-hoc analyses with Bonferroni correction will be applied when necessary. Effect sizes (partial eta squared) will be reported to assess the magnitude of differences between interventions. Additionally, Pearson or Spearman correlation coefficients will be used to explore associations between changes in hypersensitivity and secondary outcomes, depending on data distribution. Sensitivity analyses using an intention-to-treat approach may also be performed to assess the robustness of the findings. A significance level of 0.05 will be adopted for all analyses.

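### Repeated measures ANOVA is a poor fit for restoration longevity: failure is a one-way event, and failures found before 12 months would drop out of the analysis

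*Protocol article*

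**What the plan says.** All references are to the Protocol article.

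- **Objectives.** One of the two secondary objectives is: "To assess the clinical performance of the self-cure composite resin in terms of restoration longevity". The other compares the three interventions on hypersensitivity over time.
- **Clinical assessment.** On the instrument: "The criteria of the modified USPHS index will be used for the assessment". On failure: "The restoration will be characterized as a failure and the tooth will be excluded from the study", and the trigger is a C score on any criterion.
- **Clinical protocol.** Restorations are examined at 48 hours and at 4, 8 and 12 months.
- **Statistical analysis.** Repeated measures ANOVA is first assigned to the Wong-Baker and SCASS scales, with Shapiro-Wilk, Levene and Mauchly tests and a Greenhouse-Geisser correction if needed. Then: "For secondary outcomes, repeated measures ANOVA will also be used to compare differences over time among the three intervention groups". The effect measure is given as follows: "Effect sizes (partial eta squared) will be reported to assess the magnitude of differences between interventions". For description: "Continuous variables will be described with mean and standard deviation, and categorical variables by relative frequency". Intention-to-treat is optional: "Sensitivity analyses using an intention-to-treat approach may also be performed to assess the robustness of the findings".

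No survival, categorical or ordinal method is named for restoration failure.

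**The concern.** The section names a method for an outcome that it does not suit, for two reasons.

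First, a failure defined by a C score is yes or no, and it does not reverse. ANOVA compares means. Lettered grades have no natural mean, and a 0/1 failure code that can only move one way will not meet the normality and sphericity conditions the plan intends to check. Partial eta squared does not tell a reader what share of restorations survived.

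Second, the exclusion rule and the method work against each other. The event of interest ends the tooth's follow-up, and the method needs follow-up to be complete. A material whose restorations fail early would lose those failures from its own longevity comparison and so look better than it is. The Discussion presents poor restoration longevity as a main reason for studying new materials, so this comparison will be read.

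**Working it through.** The protocol states no failure rate, survival figure or sample size for longevity, so there is no figure of its own to reproduce. The calculation in the Sample size section concerns repeated measures ANOVA for hypersensitivity and does not bear on this point.

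**Step 1. Does the ANOVA sentence reach longevity?** There are two secondary objectives. Hypersensitivity over time is already assigned ANOVA in the sentence on the pain scales. Longevity is what remains for the later sentence on secondary outcomes. This is an inference, but no other reading gives that sentence an objective of its own.

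**Step 2. Which teeth have complete rows?** The visits are 48 hours, 4, 8 and 12 months. A tooth first scored C at 48 hours, 4 or 8 months has no later score. A tooth first scored C at 12 months has all its scores. Complete-row ANOVA therefore loses the first kind of failure and keeps the second.

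**Step 3. How much could this matter?** Assumptions, none of them from the protocol: true 12-month failure p; the same hazard h at each of the 4, 8 and 12 month visits; no failure at 48 hours; no other loss to follow-up.

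- Hazard per visit: h = 1 − (1 − p)^(1/3)
- Failures lost, as a share of all teeth: 1 − (1 − h)²
- Apparent failure among complete rows: (1 − h)²·h / (1 − h)² = h

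| True p | h = apparent failure | Lost before 12 months | Share of failures lost | Complete rows of 25 |
|---|---|---|---|---|
| 10% | 0.0345 | 0.0678 | 0.0678/0.10 = 68% | 23.3 |
| 20% | 0.0717 | 0.1382 | 0.1382/0.20 = 69% | 21.5 |
| 30% | 0.1121 | 0.2116 | 0.2116/0.30 = 71% | 19.7 |

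A true contrast of 10% versus 30% (20 points) would appear as 3.45% versus 11.21% (7.8 points). At 20% failure in an arm of 25, about 25 × 0.1382 = 3.5 of the 5 failures would be missing.

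**Step 4. What can 25 per arm show if every failure is kept?**

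- Precision at an assumed 85% survival: 1.96 × √(0.85 × 0.15/25) = 0.140, about ±14 points for one arm. For a difference: 1.96 × √(2 × 0.85 × 0.15/25) = 0.198, about ±20 points. These are rough symmetric limits. The exact 95% interval for 21 of 25 is 64% to 95%.
- Power for 10% versus 30%, two-sided 5%: about 42% comparing proportions. For a log-rank test, the hazard ratio is ln(0.7)/ln(0.9) = 3.39 and the expected events are 25 × (0.10 + 0.30) = 10, giving about 49%.

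**The case against.** Several counter-arguments have weight.

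- **Complete-row deletion is not written down.** True: the section gives no missing-data rule, and one may be set elsewhere. But the Mauchly and Greenhouse-Geisser steps belong to the classical form of the method, which needs complete rows. If a C score were carried forward as 0/1, the failures would stay in. The method would still rest on unsuitable assumptions and report partial eta squared.
- **Failures are recorded and can be described.** This stands. The tooth is classed as a failure before it leaves, and categorical variables get relative frequencies. Nothing says failures are omitted from those frequencies. What is missing is a suitable comparison between groups.
- **The link to longevity is inferred.** Correct, as set out in step 1.
- **Intention-to-treat may be run.** It is optional and only a sensitivity analysis, so it does not secure the result.

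A reader might go further and infer that the analysis would contain only teeth that never failed, so that apparent failure is always 0%. The documents do not support this: failures first found at 12 months keep a full row, and 0% arises only if every failure is found by month 8. Nor do they support saying that ANOVA cannot estimate failure at all, since on a 0/1 code its group means are proportions.

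**Conclusion.** The point holds as a mismatch between a stated method and the outcome it would be applied to. For longevity, repeated measures ANOVA with partial eta squared does not give a valid group comparison. In its classical form it omits every failure found before the 12-month visit. Under the constant-hazard assumption about two thirds or more of failures are lost, and a 20-point difference shrinks to about 8. Those sizes depend on assumed rates and timing: earlier failures would make the loss larger, and later ones would make it smaller.

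The conclusion rests on two inferences: that longevity is among the secondary outcomes meant, and that complete rows are required. It would be too much to say that the longevity objective gets no answer, because relative frequencies could still describe failure. The point concerns a secondary objective. The primary hypersensitivity conclusion does not depend on the sentence at issue.

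**What to change.** In the Statistical analysis section, take longevity out of the ANOVA sentence and give it its own analysis:

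- Define the outcome as first C score on any USPHS criterion, counted at the visit where it is found. Include all randomised teeth, and censor teeth lost without failure at their last visit.
- Name one method in advance. Kaplan-Meier with a log-rank test, a discrete-time or interval-censored survival model, or an exact comparison of 12-month failure proportions would each be adequate. The last also needs a stated rule for teeth lost without failure.
- Report 12-month failure or survival per group with 95% confidence intervals, and say that they will be wide at 25 per arm.
- State that a tooth's exclusion after a C score does not remove its failure from the analysis.
- Describe Group 1 versus Group 3 as a comparison of restorative systems, both with laser. Etching, adhesive and the order of steps differ as well as the resin, so it does not isolate the resin.

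The cost is a change of wording and a little extra analysis. The visit at which each failure is found is already recorded, so no new data are needed. The change will not make the longevity comparison well powered.

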### Sample size calculation

The sample size will be estimated using the G*Power software (version 3.1, Franz Faul, Unikiel, Germany) [22] for a priori repeated measures ANOVA. An effect size of 0.352, derived from the group mean dispersions reported in the literature [23], will be considered. The alpha error will be set at 0.05, statistical power at 80%, and the design includes 3 groups and 5 repeated measures. The final calculation indicates the need for 66 individuals in total, corresponding to 22 participants per group. To increase the robustness of the results and compensate for potential dropouts, the sample will be inflated by 15%, resulting in 25 individuals per group and a total of 75 participants.

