### Randomization

The participants will be randomly allocated to the different groups using block randomization. A computer-generated sequence (random.org; Randomness and Integrity Services, Dublin, Leinster, Ireland) will be used to allocate each participant to a specific group maintaining a 1:1:1 proportion (equal number of participants in all groups). Randomization will be performed in 5 blocks, with 15 participants per block, totaling 75 participants across the study. Allocation concealment will be ensured with the use of sequentially numbered sealed opaque envelopes.

Teeth selected for treatment will be randomized into three groups:

**Group 1**: Photobiomodulation + restoration with self-cure composite resin

**Group 2**: Restoration with self-cure composite resin

**Group 3**: Photobiomodulation + restoration with photopolymerizable bulk-fill composite resin

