#### Group 2 – restoration with self-cure composite resin.

Same as previous sequence (Group 1) with exception of Item 3.

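### The longevity objective concerns the self-cure restoration, but the planned three-group comparison cannot attribute a difference to it, and the one pair that can is tested at 0.0167

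*Protocol article*

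**What the plan says.** The protocol article lists as its second secondary objective "To assess the clinical performance of the self-cure composite resin in terms of restoration longevity" (Objectives). It names no comparator.

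The arms are described under Randomization and Clinical protocol. Group 1 is "Photobiomodulation + restoration with self-cure composite resin". Group 2 is "Same as previous sequence (Group 1) with exception of Item 3", and item 3 of that sequence is the laser step. Group 3 is "Photobiomodulation + restoration with photopolymerizable bulk-fill composite resin". Under Clinical assessment, a C score on any modified USPHS criterion counts as a failed restoration.

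For secondary outcomes, the Statistical analysis section states that "repeated measures ANOVA will also be used to compare differences over time among the three intervention groups", then "Post-hoc analyses with Bonferroni correction will be applied when necessary" and "A significance level of 0.05 will be adopted for all analyses". Longevity is not mentioned there by name. I read it as one of the secondary outcomes because it is the subject of a secondary objective. No pair of groups is tied to that objective.

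**The concern.** The objective is about one factor, the restorative material, while the stated analysis compares three groups that differ in two factors, material and laser. Two things follow. A significant three-group result on longevity could come from the laser alone. And the pair that does bear on the material is tested as one of three, at a third of the usual significance level, although the objective needs only that pair. With 25 children per arm and a sample size set for hypersensitivity, the trial has little power to spare on longevity.

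**Working it through.** **1. What each pair compares** (Randomization; Clinical protocol for Groups 1 to 3)

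| Pair | Laser differs | Restorative system differs |
|---|---|---|
| Group 1 v Group 2 | yes | no |
| Group 1 v Group 3 | no | yes |
| Group 2 v Group 3 | yes | yes |

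Only Group 1 v Group 3 bears on the restoration without an assumption about the laser. It compares systems and not resins alone: Group 3 also has acid etching of enamel and a different adhesive.

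**2. The plan's own figure.** The only calculation given is the sample size, from "An effect size of 0.352, derived from the group mean dispersions reported in the literature", with alpha 0.05, power 80%, 3 groups and 5 measures. As a group-by-time test by the multivariate approach (df1 = 8, df2 = 2(N − 5), λ = 2N × 0.352²), N = 65 is the smallest total reaching 80%, which rounds to the stated 66. At N = 66, λ = 132 × 0.1239 = 16.4 and power is 81%. So the stated figure reproduces, but it concerns hypersensitivity. No power is given for longevity.

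**3. Inputs for longevity.** From the document: 25 per arm (no dropout, so a best case), alpha 0.05, and three pairs, so 0.05/3 = 0.0167. Failure rates are not in the document; those below are assumptions, shown as a range. Failure by 12 months is treated as yes or no.

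**4. Formulas**, with n = 25 and p̄ the overall failure proportion of the groups compared:
- Three-group test: X² = Σ(xᵢ − n p̄)² / [n p̄(1 − p̄)] on 2 df, critical value 5.99.
- Pair: z = (p₃ − p₁) / √[p̄(1 − p̄) × 2/25], critical value 1.960 at 0.05 and 2.394 at 0.0167.
- The probability of a positive result is the sum of the binomial probabilities of all outcomes that exceed the critical value.

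An example of what the adjustment does: take 1 failure of 25 in Group 1. With 6 in Group 3, p̄ = 7/50 = 0.14 and z = 0.20/√(0.14 × 0.86 × 0.08) = 2.04, significant at 0.05. At 0.0167, 7 failures (z = 0.24/√(0.16 × 0.84 × 0.08) = 2.31) are not enough and 8 are needed (z = 0.28/√(0.18 × 0.82 × 0.08) = 2.58).

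**5. Only the laser matters** (5% failure in Groups 1 and 3)

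| Group 2 failure | Three-group test positive |
|---|---|
| 10% | 7.5% |
| 15% | 19% |
| 30% | 73% |

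In all three rows Group 1 v Group 3 is positive in 2% of trials at 0.05 and in about 0.1% at 0.0167. Pooled Groups 1+2 v Group 3 is positive in 32% in the last row, so pooling is clean only if the laser has no effect on longevity.

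**6. Only the restorative system matters** (same failure rate in Groups 1 and 2)

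| Self-cure v bulk-fill failure | Three-group test | Group 1 v 3 at 0.0167 | Group 1 v 3 at 0.05 | Share of the pair's power lost |
|---|---|---|---|---|
| 5% v 20% | 37% | 15% | 38% | 1 − 15/38 = 61% |
| 10% v 30% | 45% | 23% | 45% | 1 − 23/45 = 49% |
| 5% v 30% | 73% | 46% | 71% | 1 − 46/71 = 35% |
| 10% v 40% | 77% | 53% | 73% | 1 − 53/73 = 27% |

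**7. Check on a continuous score** (noncentral F and t, 25 per arm). For a difference of 0.5, 0.8 or 1.0 SD, Group 1 v Group 3 has 25%, 65% or 86% power at 0.0167 and 42%, 80% or 94% at 0.05. The direction is the same, and the loss shrinks as the effect grows.

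**8. Precision of the self-cure failure rate** (Wilson 95% interval, assumed 12% failure). One arm, 3/25: 4% to 30%. Both self-cure arms, 6/50: 6% to 24%.

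**The case against.** The strongest reply is that the plan does not stop at the three-group test. Its post-hoc set contains Group 1 v Group 3, and in the laser-only scenarios that adjusted pair is almost never positive. A reader might infer that the plan would lead to false claims for the resin; the document does not support that, because the error requires stopping at the overall test. This stands. What remains is that the plan does not say which pair answers the objective.

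A laser effect on restoration failure is also hypothetical. The Introduction describes the laser as acting on nerve transmission, cell regeneration and inflammation. The 73% needs a 25-point laser effect on failure; at 5 points the figure is 7.5%. This stands too, and is why the range is shown.

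The objective names no comparator and could be met descriptively, and an article may leave a named contrast to the full protocol, which is cited as a supporting file. But the article does state a comparative method for secondary outcomes. The point is that this method fits the objective poorly, not that detail is missing.

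The calculations use tests of a yes/no failure, while the plan specifies repeated measures ANOVA. They illustrate the mismatch and do not measure the stated test; the logic of which groups share a resin holds for any test. Power also stays modest after the fix: with Fisher's exact test, the single contrast has about 20% at 5% v 20%.

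Finally, dropping Bonferroni could look like trading error control for power. With one contrast named in advance for this outcome, there is nothing within the outcome to adjust for, provided that the other pairs are labelled exploratory.

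**Conclusion.** The concern holds in a limited form. A three-group longevity result cannot by itself be attributed to the self-cure restoration, because two of the three arms share it. The pair that can be so attributed is already planned, but testing it as one of three costs between about a quarter and three-fifths of its power over the failure rates assumed here, with no gain for this objective.

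A reader might go further and infer that the resin question loses most of its power. The figures do not support that. The three-group test has about the same power as the unadjusted pair (37% v 38%, and 73% v 71%); the loss is confined to the adjusted pair, and it exceeds half only for the smallest effect shown.

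These sizes rest on 25 evaluable teeth per arm, on assumed failure rates, and on reading longevity as one of the secondary outcomes. The plan's approach is conservative rather than invalid, so this is a cheap improvement.

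**What to change.** State before analysis that the longevity objective is answered by a single contrast, Group 1 v Group 3, tested at 0.05. Describe it as a comparison of restorative systems. A model with one indicator for the laser and one for the restorative system gives the same estimate in this three-arm design.

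Report the self-cure failure proportion with its confidence interval from Groups 1 and 2 together and by arm. Give pooled Groups 1+2 v Group 3 only as a supportive analysis, labelled as assuming no laser effect on longevity.

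The cost is analysis wording: no extra children, visits or data. The downside is that Group 2 does not enter the main longevity contrast, and the other pairs become exploratory for this outcome.

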## Discussion

Molar incisor hypomineralization exerts a negative impact on the lives of affected individuals. The search for effective conservative treatment to ensure the reduction in hypersensitivity, preservation of the tooth structure and longevity of the restoration seems to be the most adequate choice for teeth that require early treatment [28].

Teeth with MIH can remain hypersensitive even after restorative treatment. Therefore, effective pain control is indispensable for the clinical success of the restoration and improvement in the patient’s quality of life [31].

Inadequate restoration longevity in teeth with MIH is a limitation of the treatment and one of the main challenges that dentists face. Besides the additional financial expenses, the need for constant retreatment can cause emotional exhaustion in patients [32]. Thus, there is a need for a better understanding of the real effect of novel materials that provide effective long-term treatment.
